### Study setting

The Integra Initiative selected Kenya, a medium-prevalence HIV country, and Swaziland, a high prevalence HIV country as contrasting settings where a partial evidence base existed to build on, and where Integra Initiative partners already had experience in working. The FP model of integration will be implemented in Central Province in Kenya, where facilities serve a population with a high modern method contraceptive prevalence rate (58%) compared with the national average (33%) [24], and slightly lower HIV prevalence (7.6%) among women aged 15 to 49 years in Central Province compared to the national level (8.7%) [25]. The PNC model will take place in Eastern Province in Kenya where facilities serve a population with a relatively high modern method contraceptive prevalence rate (48%), and relatively low HIV prevalence (5%) among women aged 15 to 49 years. The national HIV prevalence among pregnant women is 9.7% [25]. In Swaziland the PNC model of integration will take place in facilities that serve a population with a relatively high modern method contraceptive prevalence rate (48%), compared to 36% nationally; a similar HIV prevalence among women aged 15 to 49 years (31%) compared to national average of 26%, and 39% among pregnant women compared to the national rate of 38% [26].

### Methods/Design

#### Approach and conceptual framework

The implementation environment for the Integra Initiative is complex, with government policies and practices around integration in constant development. The Integra Initiative therefore embeds rigorous evaluation research within the ‘reality’ of government commitment to large-scale delivery of integrated HIV and SRH services, and to use the findings to strengthen ongoing service provision at each site. The Integra Initiative has developed a conceptual framework (Figure 3) to guide its evaluation, based on a logic model encompassing inputs, processes and outcomes, as well as the wider community and policy context. This model encompasses different components and processes of integration, ranging from readiness and service infrastructure, delivery, utilization and outcomes along with the needs and perspectives of providers, clients and community members.

**Figure 3 F3:**
[figure not shown]
Integra Initiative Conceptual Framework.

There is an emerging body of literature addressing the challenges of using randomized controlled trials to assess the impact of public health interventions [27-29]. Particularly in cases such as the Integra Initiative, where the causal chain between intervention and outcome is long, where there is a broad range of outcomes that need to be explored, and where there is already a degree of integration occurring in some clinic settings, attempting to conduct a randomized controlled trial is not appropriate [27-29]. Consistent with evaluation designs described by Habicht and colleagues [27], the Integra design includes evaluation of performance and impact to try to make two types of causal inference: adequacy and plausibility. Evaluation of adequacy will assess whether the expected changes in provision, service utilisation and cost-effectiveness have occurred in intervention facilities (Columns 1 & 2 of the logic model). Evaluation of impact will assess the plausibility that changes in service, health and behavioral outcomes (Columns 3 & 4) are due to the Integra Initiative. The case for such plausibility will be built from the following strands of evidence:

• Comparing findings in ‘intervention’ facilities with those in facilities chosen as ‘comparison’ sites prior to the evaluation

• Exploring a dose–response relationship between the measured extent of integration and the study outcomes

• Measuring changes in performance over time, to demonstrate a logical sequence between the intervention (integration) and outcomes

• Measuring change in each step of the logic model – a prerequisite for any attribution to the intervention

• Triangulating findings from a mix of research methods to capture a range of perspectives and insights from different disciplines

The study will employ a controlled pre- and post-test quasi-experimental, or non-randomised, design. Since the research is being conducted in real-life health delivery settings where programmatic contamination is possible due to ongoing health programme interventions over the study period, the control group will be referred to as a ‘comparison group’, for which outcomes will be compared over time up to two years after implementation.

#### Selection of intervention study sites

The study will be implemented in public health facilities in Central and Eastern provinces in Kenya and in three regions in Swaziland. Six intervention facilities from two districts in Central Province were selected from the original 23 facilities participating in the previous integration study using FP as the entry point [30] and building on that experience. The two criteria for selecting intervention facility selection were: i) good performance in the previous study and ii) high throughput of FP clients (≥100/month). These six intervention facilities include two hospitals and four health centres. In order to match these sites with six comparable sites in the same province and avoid contamination, additional criteria (see below) were used to randomly select facilities with similar characteristics from outside the two original study districts.

The existing four facilities (public health units/MCH-FP) from the previous study in Swaziland [31] were selected as the intervention facilities. In order to match these sites with four comparable sites and avoid contamination, criteria were used to select the comparison facilities that have similar characteristics but away from original study sites. Sites that fitted the criteria (see below) were visited in July 2008 by Population Council, London School of Hygiene & Tropical Medicine (LSHTM) and the MOH and assessed for comparability to the intervention sites. In discussion with the Provincial Health Management Team for Eastern Province, Kenya we were advised not to continue with the district from the previous study [20]. This was due to the high number of other health sector interventions. Therefore, two districts with limited external support were selected and randomly allocated as intervention and comparison sites.

#### Selection of comparison study sites

To maximize equivalence between the intervention and comparison facilities, thereby minimizing selection bias, a pair-wise matching sampling design will be used. Comparison facility selection will be based on four criteria, namely: high client load (> 50 infants/month receiving their first immunizations at 6 weeks at the PNC-HIV clinics and >100 FP clients/month at the FP-HIV clinics); a minimum of two providers qualified in and currently delivering FP services; a range of services available (FP, voluntary counseling and testing (VCT), STI treatment, prevention of mother-to-child transmission (PMTCT); and no current provision of fully integrated PNC-HIV and FP-HIV services. Facilities allocated to each study model serve populations with similar socio-economic characteristics, have a similar health infrastructure (i.e. public sector), and serve a population with a relatively high modern method contraceptive prevalence rate and similar HIV prevalence among women aged 15 to 49 years. To minimize contamination, the facilities’ (with comparable characteristics) will be selected in different districts in the same province. The number of facilities that will be purposively selected for each model and country are summarized in Table 2.

**Table 2 T2:** Sampling strategy and sample size calculations for each Integra research component

**Research Component**	**Sampling strategy**	**Key indicators used in sample size calculation**	**Adjustments to sample calculation**	**Model 1. Kenya FP**	**Model 2. Kenya PNC**	**Model 2. Swaziland PNC**
Sampling of facilities	Theoretical sampling to point of saturation within province	4 criteria: high client load; minimum of 2 FP providers; range of SRH services available; no current provision of SRH-HIV integration	n/a	12 facilities: 6 Intervention and 6 Comparison	12 facilities: 6 Intervention and 6 Comparison	8 facilities: 4 Intervention and 4 Comparison*
HFAs: Facility inventory				1 per facility	1 per facility	1 per facility
HFAs: Client exit interviews & linked observations of consultations	Consecutive sample and saturation	Quality of Care analysis 6 CPIs	No	18 per facility: 6 new clients, 6 repeat clients and 6 clients switching FP method	6 within 48 hours postpartum 6 at one week and 6 at 6 weeks per facility	6 within 48 hours postpartum 6 at one week and 6 at 6 weeks
HFAs: Structured interviews with providers	Convenience	All providers working in MCH-FP units	No	3-6 providers per facility	3-6 providers per facility	3-6 providers per facility
HFAs: Client flow assessment	Census over 5 days based on existing client load		No	50 – 200 clients per day	50 – 200 clients per day	50 – 200 clients per day
Cohort	Consecutive sample of female clients (recruited if within 12 weeks post-partum in PNC facilities)	Kenya: 80% power to detect a 5% increase in condom use, among all women in PNC and those using other contraceptive methods in FP facilities.	1952 clients: 976 from Intervention and 976 from Comparison facilities			
	Swaziland: To detect a 7% increase in condom use among PNC clients.	30% loss to follow up; over-sampling of HIV-positive clients until min of 400 in Intervention & Comparison facilities	1978 clients: 989 from Intervention and 989 from Comparison facilities			
Household survey	3-stage cluster survey design, for random selection of EAs, households and individuals	80% power to detect 10% increase in % of women who have ever used study facility.	Design effect of 2.0	1632 (816 male; 816 female) within 10km catchment area of FP facilities	n/a	816 (408 male; 408 female) within 10km catchment area of PNC facilities

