A three-stage cluster survey design will be employed. The primary sampling units (PSUs) will be census enumeration area (EAs), and the sampling frames will comprise the catchment areas of the relevant facilities (≤10km radius). Firstly, probability proportional to size (PPS) sampling will be used to randomly select EAs, with sampling frames derived from national censuses. It is estimated that between 25 and 40 EAs will be required to achieve the sample size in each survey district. Secondly, a random sample of households will be selected within each EA, using a systematic approach to achieve full geographic coverage of the EA based on estimated household numbers. Thirdly, one person will be randomly selected using a household roster to determine the sampling frame of eligible household members. The sample size calculations are displayed in Table 3, and were determined by measurement of the following key outcomes: (i) % respondents who have used a study facility (ii) % who can list the SRH/HIV services available at study facilities, (iii) % of female respondents using multiple services vs an integrated service, and (iv) % of female respondent’s not using modern contraception. The sample calculations were based on 80% power and a design effect (DEFF) of 2.0 to account for clustering, as well as accounting for non-response.

f) Qualitative study

In-depth interviews (IDIs) will be conducted to explore key study themes in greater depth. Respondents will be a sub-sample of cohort clients; health providers in study facilities; and a sub-sample of respondents from household surveys. The purpose of the in-depth interviews with the cohort clients is to explore experiences and motivations for use of services, facility switching, stigma and any other issues that arise after initial quantitative analysis. The purpose of the interviews with healthcare providers is to identify clinic- and provider-specific issues that may affect the delivery of integrated care. Interviews will aim to establish providers’ expectations regarding integration, to develop an in-depth understanding of their ongoing experience with providing integrated SRH-HIV services, attitudes towards PLWH, and to explore specific issues of workload, supervision and support, emotional strains, satisfaction and clinical records.

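### The household survey's 80% power is stated for women in Table 2 but for all respondents in the text, and 408 women per area support it only at low or high baselines

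*Protocol article*

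**What the plan says.** In the protocol article, Table 2 (under Selection of comparison study sites), the household survey row gives the basis for the sample size as "80% power to detect 10% increase in % of women who have ever used study facility", adjusted by "Design effect of 2.0". The planned samples are:

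- Kenya: "1632 (816 male; 816 female) within 10km catchment area of FP facilities"
- Swaziland: "816 (408 male; 408 female) within 10km catchment area of PNC facilities"

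Section e) Household surveys (under Description of methods and data collection) lists four outcomes that determined the size. The first is "i) % respondents who have used a study facility", with no restriction to women. The third and fourth are restricted to female respondents. The section adds: "The sample calculations were based on 80% power and a design effect (DEFF) of 2.0 to account for clustering, as well as accounting for non-response".

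The same section says that Kenya is surveyed in two districts, one with intervention and one with comparison sites, and Swaziland in one town that contains both kinds of site. The abstract describes the surveys as taking place before and after the intervention. The article gives no baseline proportion, significance level or non-response rate for this calculation.

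**The concern.** Table 2 and the text name different populations for what is evidently the same indicator, and the sample is half women and half men. The change of population therefore halves the number of people available. If the calculation was made for respondents of both sexes and then labelled as women, the published power does not describe the women-only comparison.

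The household survey is the study's population-level evidence on use of the facilities and demand for services. A reader who trusts 80% power among women would give too much weight to a null result in that group.

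**Working it through.** **Inputs from the article.** Power 80%; increase of 10%, read here as 10 percentage points; design effect (DEFF) 2.0; 816 people (408 women) in Swaziland; 1632 people (816 women) over two Kenyan districts.

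**Assumptions.** Two-sided 5% test, two equal groups, equal split of the Kenyan sample between districts (1632/2 = 816 people, 816/2 = 408 women per district). The baseline is varied because none is stated.

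**Step 1: reproduce 816.** For baseline p1, p2 = p1 + 0.10 and mean p̄, the number per group before clustering is

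n = [1.960·√(2p̄(1−p̄)) + 0.842·√(p1(1−p1) + p2(1−p2))]² / 0.10²

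At 50% v 60%: (1.960 × 0.7036 + 0.842 × 0.7000)² / 0.01 = 387.3. The continuity correction, (n/4)·[1 + √(1 + 4/(n × 0.10))]², gives 407.1, rounded up to 408. Then 408 × 2.0 = 816 per group.

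This equals the total of both sexes in Swaziland and in each Kenyan district. It is not the only route to 816. Without the correction, 388 × 1.05 = 407.4, rounded up to 408, and × 2.0 = 816, which includes about 5% for non-response. Both routes use a mid-range baseline and count both sexes.

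**Step 2: power for women.** With 408 women per group the effective number is m = 408/2.0 = 204, and

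power = Φ{[0.10·√m − 1.960·√(2p̄(1−p̄))] / √(p1(1−p1) + p2(1−p2))}

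At 50% v 60%: (1.428 − 1.379)/0.700 = 0.070, and Φ(0.070) = 0.53. The result is the same for a baseline and its mirror image.

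| Baseline (10-point rise) | Women needed per group, DEFF 2.0, uncorrected | Power with 408 women per group |
|---|---|---|
| 10% or 80% | 398 | 81% |
| 15% or 75% | 500 | 72% |
| 20% or 70% | 588 | 65% |
| 30% or 60% | 712 | 56% |
| 40% or 50% | 776 | 53% |

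**Step 3: detectable difference.** Solving the same formula for the increase that gives 80% power with m = 204 yields about 10 points at a 10% baseline, 12 at 20%, 13 at 30% and 14 at 40% or 50%.

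**Step 4: other readings of the contrast.** With 816 per group (m = 408), power at 50% v 60% is 82%. This applies to respondents of both sexes in one area. It also applies to Kenyan women if the contrast is before against after with both districts pooled, because 816 women are then available at each round.

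**The case against.** The strongest reply is that Table 2 may be true as written. With no stated baseline, a sizing on women at 10% v 20% needs 398 per group against 408 planned. A matching number of men could then have been added. The same holds at 80% v 90%. This stands: a reader might infer that 816 is reached only by counting men, or that women have half the sample they need, but the article does not establish either. The exact match at 50% v 60% suggests a both-sexes calculation and does not prove it.

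A reader might also infer that 816 leaves nothing for non-response. That is not shown, since 388 × 1.05 × 2.0 reaches the same figure with an allowance included.

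Third, the article does not say which contrast was powered. For a before-after contrast pooled over the Kenyan districts, the women alone suffice. This also stands, and it limits the Kenyan part of the point. That contrast does, however, set aside the intervention-against-comparison structure on which the design section builds its case for plausibility. Nor should power be reported against the plan for a before-after-by-district contrast, which the article does not claim to power.

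Finally, an article may leave the baseline, significance level and non-response rate to the full protocol. Their absence is not criticised here. What remains is that two published statements of one sizing indicator disagree on the population.

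**Conclusion.** The point holds in limited form. Table 2 and the household survey section disagree on whether the indicator is measured in women or in all respondents, and the number available differs by a factor of two. With 408 women per group, the stated 80% power for a 10-point rise is met at a baseline of about 10% or below, or 80% or above. It fails over roughly 15–75%, falling to about 53% at 40–50%. This covers the Swaziland survey taken as one area, and between-district or single-district contrasts in Kenya. It does not cover a Kenyan before-after contrast pooled over both districts.

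The figures rest on a two-sided 5% test, a 10-point reading of the increase, an equal split between the Kenyan districts, the article's DEFF of 2.0, and no further loss to non-response. It is a correction to a stated power, not evidence that the survey is too small for its purpose.

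**What to change.** Make Table 2 and section e) name the same population, in one of two ways:

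1. **Respondents.** Change Table 2 to state the 80% power for respondents of both sexes. With 816 per group this gives about 82% at a 50% baseline before any non-response. The third and fourth sizing outcomes remain women-only, so they should not be read as covered by this statement.
2. **Women.** Keep women in Table 2, change the first outcome in section e) to match, and replace the claim with the difference detectable at 80% power with 408 women per group: about 14 points at a 50% baseline, or the corresponding figure for the baseline the investigators used.

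Either way, the sentence should say which contrast the power refers to, since for Kenya that decides whether 408 or 816 women count. The cost is a change of wording in one table row and one paragraph. No extra interviews are needed.

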***Qualitative – in-depth interviews***						
Providers	Convenience sampling			1-3 providers per facility	1-3 providers per facility	1-3 providers per facility
Cohort clients	Purposive sampling to reflect issues emerging from quantitative data		25 HIV-positive clients; and 25 other clients	25 HIV-positive clients; and 25 other clients	25 HIV-positive clients; and 25 other clients	
Community members	Purposive sampling to reflect issues emerging from quantitative data		20 men	n/a	20 men	

* 2 facilities subsequently added due to lower than expected client load at comparison sites.

#### Overview of study components

In order to address the objectives, the study will include three levels of analysis. The first unit of analysis will be the facility level. Facility-based research will be conducted at four stages during the study in order to track changes over time in clinic preparedness for the range of services offered, service integration and utilization, quality of care indicators, client satisfaction, costs and efficiencies of service provision. Health Facility Assessments (HFAs) will collect comparable data across clinics, incorporating the following methods: facility checklists, structured observations of client provider interactions (CPI), client exit interviews, health care provider interviews, client flow analysis, routine program and costing data analysis. The second unit of analysis will be the client level and will involve research to understand how the demand for and use of SRH and HIV services is shaped by the changing structure and performance of facilities, and how integration impacts upon client SRH and HIV-related behaviours. This will be done through a variety of methods, including: client exit interviews and a cohort study of clients to assess how individual outcomes are shaped by the services accessed (including fertility intentions, unintended pregnancy, use of FP, HIV status, STI/HIV-related behaviors and health seeking behaviors). In depth interviews will also be conducted with a sub-sample of cohort clients to explore experiences and motivations for use of services, facility switching, stigma and other issues arising from initial quantitative analysis. The third unit of analysis is the population level, which will involve household surveys within communities living in the catchment areas of selected study facilities. This will allow comparison of the characteristics, behaviour and attitudes of clients *vs.* non-clients, as well as offering insights into demand for and use of for vertical or integrated services and reasons for use/non-use of these. In-depth interviews (IDIs) and focus group discussions (FGDs) with groups of men comprising service users and non-users will also be conducted. These qualitative interviews with community members can allow more detailed exploration of reasons for service-use patterns, choice of facilities and reasons for non-use.

#### Sampling and indicators

Details on research methods are provided below; sampling strategy and sample size calculations for each method are summarised in Table 2.

The operational results (outcomes) and the main indicators that will be measured and analysed for each study objective are shown in Table 3.

**Table 3 T3:** Operational results and indicators to be used to compare results from the intervention and comparison health facilities

**Objective 1. Determine the benefits of different integrated models to increase range, uptake and quality of selected SRH and HIV services and to diversify the profile of clients.**		
**Results/Outcomes**	**Indicators**	**Data source**
Feasibility of linking services demonstrated	Number of internal and external referrals, Number of staff updated in HIV counseling and testing Number of staff updated in HIV BCC prevention, Facilities have adequate equipment and supplies	Service statistics Provider interviews Facility inventory
Provision of linked services to clients	Clients received CT in FP consultation, Clients referred for ART, Clients referred for other services, Number of referrals attended, Proportion of population demanding integrated services, Proportion of population accessing integrated services, Proportion of services users giving integration as a reason for choice of clinic	Client exit Provider interview Cohort Community Survey
Increased % of eligible HIV+ women starting to use ART	Proportion of women reaching referral site clients know their CD4 counts	Service statistics Cohort
Increased uptake of range of SRH services including integrated CT, FP, PNC and STI screening services	% FP clients accessing more than one service Proportion of population accessing more than one service at last FP or PNC visit	Service statistics Exit /Cohort Community Survey
Increased quality of a range of SRH services	% clients receiving minimum level of quality services	Client – provider interaction, exit interview
Increase in number and diversity of clients	% men and women using component services Proportion of clients using component services by age, SES and gender	Community Service Statistics Client exit /CPI
Increased numbers of clients screened/managed for STIs	% FP clients accessing separate/integrated services	Service statistics Client Flow Cohort
Increased in new and repeat FP clients testing for HIV		Service statistics Cohort
Improved attitudes of service providers towards HIV+ clients	% Providers indicating non discriminatory attitudes % Clients recommending services to others	Provider interview Cohort survey Community Survey
**Objective 2. Determine the impact of different integrated services on changes in HIV risk-behavior; HIV related stigma and unintended pregnancies.**		
Reduction in reported HIV risk behaviors among HIV negative & HIV positive clients	Condom use at last sex; Number of partners in past 12 months Received STI/HIV counseling Consistent condom use reported Use of condoms with another FP method (dual protection)	Cohort Client Exit Community Survey
Reduced incidence of unintended pregnancies	% women who become pregnant (incidence) % women reporting planned pregnancy % women with correct knowledge of fertile period % of population who report unintended pregnancy in last 12 months	Cohort Client Exit Community Survey
Increased duration of contraceptive use among HIV negative & HIV positive clients	Ever/current use of FP method Discontinuation FP rates in 12 months Ability to achieve fertility goals	Cohort survey
Improved attitudes of service providers towards HIV+ clients	Proportion of providers indicating non discriminatory attitudes towards HIV positive clients	Provider interview
Reduced stigma at health facilities.	Clients reporting positive experience of CT process % clients reporting unacceptable stigmatizing behavior by providers	Community and Cohort survey
Decreased stigmatization at community level of HIV services if integrated with FP RH services	Perceived barriers to accessing services: costs, distance, quality, waiting times, stigma surrounding service	Community survey Cohort survey
**Objective 3: Establish the efficiency of using different operational models for delivering integrated services in terms of: cost, utilization of existing infrastructure and human resources.**		
Total resource requirements and unit costs of intervention	Cost per eligible client receiving ART, Cost per person-month of receiving ART Cost per client counseled, tested and receiving results Cost per client receiving each service component	Economic study

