### Definition and types of integration models

For the purposes of this study integration is defined as offering clients two or more services in the same visit. To better understand how services can be integrated in different countries, this study focuses on two key models of integration in Kenya and Swaziland. The first model focuses on integration of FP and HIV services (integrated FP model) and entails performing HIV testing, STI screening and management, cervical cancer screening, condom promotion within FP consultations, as well as active referral to antiretroviral (ART) units for HIV-positive clients (Figure 1). The FP model will be evaluated in Kenya only.

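### Table 3 names ART initiation among eligible HIV-positive women as an outcome, but neither indicator in that row measures it

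*Protocol article*

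**What the plan says.** The section Sampling and indicators gives Table 3 a definite status: "The operational results (outcomes) and the main indicators that will be measured and analysed for each study objective are shown in Table 3". The table's title adds that the indicators serve to compare intervention with comparison facilities.

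Under Objective 1, one outcome is "Increased % of eligible HIV+ women starting to use ART". Its indicator cell reads "Proportion of women reaching referral site clients know their CD4 counts", which is most naturally two items: the share of women who reach the referral site, and clients' knowledge of their CD4 count. The row's data sources are service statistics and the cohort.

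ART receipt itself is named in Objective 3, as a unit cost from the economic study: "Cost per eligible client receiving ART", followed by a cost per person-month on ART.

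Under Objective 2, the outcome of reduced reported HIV risk behaviour has five indicators. Part of that cell reads "Number of partners in past 12 months Received STI/HIV counseling Consistent condom use reported". The other two are condom use at last sex and use of condoms together with another family planning method.

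**The concern.** An indicator should be able to stay flat when its outcome is flat. The two ART-row indicators need not. Table 1 (Description of intervention) has HIV-positive family planning clients sent to the laboratory or ART unit for blood tests, and strengthens the referral link between reproductive health clinics and ART centres, with new referral forms in Kenya. The postnatal model also includes referral of HIV-positive mothers to HIV services. Successful delivery of these components raises attendance at the referral site and knowledge of CD4 counts almost by construction, whether or not more eligible women start treatment.

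At stake is one of the few outcomes in Objective 1 that lies close to patient benefit. Following the table, the study could claim better ART uptake from data that show only that the referral step was carried out.

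The counselling item raises the same issue on a smaller scale. It is a service received, listed as evidence of changed behaviour.

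**Working it through.** No figure in the plan has to be reproduced, and no power or sample-size formula applies. The check compares each outcome with its indicators.

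**ART row**

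| Element | Outcome as named | Indicator 1 | Indicator 2 |
|---|---|---|---|
| Event | Starting ART | Reaching the referral site | Knowing a CD4 count |
| Denominator | Eligible HIV-positive women | Women, not further specified | Clients, not further specified |
| Can rise through the referral component alone | Not by itself | Yes | Yes |

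Result: 0 of 2 indicators measure the named event, and 0 of 2 state the named denominator.

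The gap can be written as an identity. Among eligible HIV-positive women, let R be reaching the referral site and S be starting ART. Then

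P(S) = P(R) × P(S given R) + [1 − P(R)] × P(S given not R).

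Even if indicator 1 were restricted to eligible women, it would give only P(R). A difference in P(R) between arms says nothing definite about P(S) unless P(S given R) and P(S given not R) are also known, and no indicator in the row supplies either. A woman who attends only for a blood test adds to indicator 1. A woman who knows her count adds to indicator 2 whatever its value, whether or not she is eligible.

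**Does another row close the gap?**
- Referral for ART appears under provision of linked services. It counts referrals, a step even earlier than reaching the site.
- The Objective 3 unit costs need a number of eligible clients receiving ART. They are cost ratios, not an uptake comparison between arms. Receiving ART also includes women already on treatment, so it is not the same as starting.

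No row of Table 3 reports initiation among eligible women.

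**Risk-behaviour row**

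| Indicator | Reported behaviour? |
|---|---|
| Condom use at last sex | Yes |
| Number of partners in the past year | Yes |
| STI/HIV counselling received | No, service delivered |
| Consistent condom use | Yes |
| Condoms with another method | Yes |

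Result: 4 of 5 measure behaviour and 1 of 5 measures delivery. HIV counselling is part of the strengthened package in Table 1 for both models, so this one item can rise with no change in behaviour.

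**The case against.** The best defence of the ART row is that the article condenses a fuller protocol in which indicator definitions would sit, that reaching the referral site is a real step in a model built on active referral, that Objective 3 already implies data on eligible clients receiving ART, and that ART start is not a sizing outcome for the cohort. Much of this is fair, and it limits how serious the point is. It does not remove it. The article does not leave the indicator to another document. It states a pairing and calls these the main indicators, and the pairing does not match. That the data may be collected anyway makes the correction cheap, but it does not make the listed indicators valid for the outcome.

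A reader might go further in three ways that the documents do not support.

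- **The uptake row.** One might infer from "FP clients accessing more than one service", together with the definition that "integration is defined as offering clients two or more services in the same visit", that any two services count as integration and that an SRH-HIV effect could be missed. But the population indicator is tied to the last family planning or postnatal visit, and HIV counselling and testing within the family planning consultation has its own indicator. The household survey section separates using multiple services from using an integrated one. Data management and analysis builds an index of integration as the exposure for the dose-response analysis and to adjust for baseline differences. The documents give no figure for how often standard visits already include two services, and Table 1 remarks that standard care seldom follows the guidelines at facility level.
- **The STI row.** The outcome "Increased numbers of clients screened/managed for STIs" appears beside an indicator that does not mention STI. In the available text, the indicator cell of the next row is blank, so a merged cell is possible and the alignment is too uncertain to rely on.
- **Risk behaviour judged by counselling.** Four of the five indicators are behaviours, no composite is specified, and the cohort is sized on reported condom use (5% to 10% in Kenya, 13% to 20% in Swaziland). Counselling alone could not produce the Objective 2 conclusion.

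**Conclusion.** The point holds for the ART row and should be corrected: the outcome is initiation among eligible HIV-positive women, and 0 of its 2 indicators measure that. The conclusion rests on reading the indicator cell as two items. If it is read as one run-on item, it still contains no ART start and no eligible denominator. The size of any misleading difference cannot be computed, because the documents give no rates of referral attendance, CD4 knowledge or ART initiation.

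The counselling item is minor: 1 of 5 indicators is in the wrong place, and the behavioural outcome is otherwise properly covered.

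Nothing here affects the sample size, the condom-use or unintended-pregnancy outcomes, or the integration index. It is not evidence that Table 3 as a whole fails to measure integration.

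**What to change.** In the ART row of Table 3, make the indicator the percentage of ART-eligible HIV-positive women who started ART, by arm, with eligibility and the period for starting defined. Keep reaching the referral site and knowing a CD4 count, labelled as process steps and each with its denominator stated. Service statistics and the cohort are already the row's sources, and Objective 3 already requires eligible clients on ART to be identified. What may be missing is the number of eligible women who have not started, and the date of starting for those who have. The cost is a table edit and possibly one added cohort question.

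Move the counselling item to Objective 1 and report it as service delivery, not as evidence of behaviour change. This is an edit to the table only and needs no new data.
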